#### Additional analysis

We will use log-binomial models to evaluate the relative risk of AD with respect to important demographic and reproductive variables (e.g., age, and parity), COVID-19 related concerns, and gender role burden (e.g., time spent in childcare and domestic tasks). We will evaluate these variables as risk factors for AD development and exacerbation. In the unlikely event that none of the assessed screening tools meets the standard of a sufficiently accurate measure, data from the first assessment will be used to empirically derive a new measure. This would involve exploratory and confirmatory factor analysis, followed by logistic regression and prediction modelling, using the screening tool items from the first assessment as training, and the second assessment as testing and validation.

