**Methods:**

A large, prospective cohort of pregnant people (*N* = 1,000) is being recruited proportionally across health service delivery regions in British Columbia (BC). The screening accuracy of a broad range of perinatal AD self-report measures are being assessed using gold standard methodology. Consenting individuals are administered online questionnaires followed by a semi-structured diagnostic interview between 16- and 36-weeks’ gestation, and again between 6 and 20 weeks postpartum. Questionnaires include all screening measures, measures of sleep and unpaid family work, and questions pertaining to demographic and reproductive history, COVID-19, gender role burden, and mental health treatment utilization. Interviews assess all current anxiety disorders, as well as obsessive–compulsive disorder, and posttraumatic stress disorder.

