## Methods

### Study design

The current study employs a prospective cohort design.

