### Procedures

Following study enrollment, participants are administered questionnaires and an interview at two time points: once prenatally and once postpartum. Each assessment consists of online questionnaires and a semi-structured diagnostic interview. Participants are emailed a link to the questionnaires which they complete online. Prenatal questionnaires are completed between 16- and 32-weeks’ gestation. Postpartum questionnaires are completed between 6 and 16 weeks postpartum. All interviews are conducted over the phone or by video conference, 2–6 weeks after the completion of the questionnaires. See Fig. 1 for diagram of participant flow through the study.

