#### Diagnostic interviews

##### **Diagnostic Assessment Research Tool (DART)** [90]

The DART is a psychometrically sound, semi-structured diagnostic interview designed to assess of a wide range of mental health conditions within the Diagnostic and Statistical Manual of Mental Disorders – 5th edition – Text Revision (DSM-5-TR) mental health conditions, including all the anxiety and anxiety-related disorders [90]. The DART includes mandatory, criterion-based questions and optional questions that may be necessary for clarification in order to make a diagnosis. Psychometric testing of the DART demonstrates excellent construct validity and good convergent and discriminant validity, and high interrater reliability [91]. The DART is used in this study to assess: (a) all DSM-5-TR anxiety disorders, (b) OCD, (c) PTSD, as well as (d) disorder age of onset and relation to reproduction. To assess perinatal AD specifically, the DART interview has been tailored to include perinatal specific examples (e.g., fear of childbirth, perinatal-related obsessions, birth trauma).

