The study includes a number of additional methodological strengths. Specifically, the study is powered to ensure we can assess the accuracy of included screening tools both for the AD as a whole, but also for each individual AD. Our approach to recruitment is designed to result in data for 1,000 pregnant and 1,000 postpartum people. We are over-sampling, where needed, perinatal people with specific AD so that we are able to report on screening accuracy for each of the individual AD.

Beyond the core goal of this research (i.e., to assess the accuracy of various self-report measures when used as screening tools for perinatal AD), we have the opportunity to explore a number of additional research questions. For example, because this research is based on DSM-5 anxiety and related disorders, we are also able to explore screening for separation anxiety disorder. To our knowledge, no findings related to screening for adult separation anxiety among perinatal people have been published. In addition to providing information about screening accuracy for adult separation anxiety disorder, we will also be able to provide the first estimate of the prevalence and incidence of this condition among perinatal people. Further, we will document the point prevalence and postpartum incidence of perinatal AD in pregnancy and the postpartum. To our knowledge, perinatal AD prevalence, based on DSM-5 criteria has yet to be reported. Further, we will be able to assess the extent to which participants who report symptoms meeting criteria for one or more AD go on to receive an assessment and treatment for these conditions. We will also assess various predictors (e.g., demographic, reproductive, identity, experience of discrimination) of perinatal AD symptoms and diagnosis, as well as assessment and treatment access and utilization. Finally, we will assess the relationship between the burden and gender distribution of unpaid domestic labour (i.e., household chores and childcare responsibilities) and mental health.

Findings from this research will provide rich data to answer not only our core research questions but additional, important questions pertaining to perinatal AD.

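### The log-binomial analysis is read as risk factors for AD development and exacerbation, but its only stated outcome is AD yes/no, with no at-risk set for onset and no measure of worsening

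*Protocol article*

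**What the plan says.** The Protocol article, under Additional analysis, names one regression for the predictor question: "We will use log-binomial models to evaluate the relative risk of AD with respect to important demographic and reproductive variables". COVID-19 concerns and gender role burden are listed as further exposures. The next sentence gives the intended reading: "We will evaluate these variables as risk factors for AD development and exacerbation". The section does not say at which assessment AD is taken, whether it means current or new disorder, or who is at risk.

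Other sections bear on this:

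- The Methods part of the Abstract describes what the interviews record: "Interviews assess all current anxiety disorders, as well as obsessive–compulsive disorder, and posttraumatic stress disorder".
- Study design and Procedures give two waves: "The current study employs a prospective cohort design", and "participants are administered questionnaires and an interview at two time points: once prenatally and once postpartum".
- The description of the DART lists "disorder age of onset and relation to reproduction" among the things it is used to assess.
- The Discussion announces that "we will document the point prevalence and postpartum incidence of perinatal AD in pregnancy and the postpartum".
- Elsewhere the predictor aim is worded more modestly. The secondary and exploratory objectives speak of exploring relationships with AD. The Discussion speaks of predictors "of perinatal AD symptoms and diagnosis, as well as assessment and treatment access and utilization".

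**The concern.** Development and exacerbation are two different estimands. Development needs a group free of AD at the start and a count of new cases afterwards. Exacerbation needs a graded measure taken twice in people who already have AD. The plan attaches both to a single yes/no outcome and sets up neither.

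If the model is fitted as literally written, to AD as the interviews record it in all participants, its ratio reflects who already had AD and who stayed ill, as well as who became ill. Some exposures, such as concern about COVID-19 or the burden of domestic work, are self-reports that existing anxiety may itself raise. Associations with long-standing AD could then be published as effects on onset or worsening.

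**Working it through.** The article gives no sample size, power or effect size for this analysis, so there is no figure of its own to reproduce. The check has two parts.

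**Comparing what each claim needs with what is stated**

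- *Development.* It needs an at-risk set without AD prenatally, and new AD as the outcome. Additional analysis states neither. The design can supply both: two diagnostic interviews, an onset item in the DART, and an announced postpartum incidence.
- *Exacerbation.* It needs an outcome that can worsen. Additional analysis states only AD yes/no, and someone with AD at both waves scores yes twice whether better, unchanged or worse. A severity score is mentioned only under Interview training, as a criterion for qualifying interviewers. Table 1 shows symptom scales such as the GAD-7 and PASS at both waves, but no section names change in any of them as an outcome.

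**How far the ratio can depart from the onset ratio if current AD is modelled in everyone**

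Inputs from the article: 1,000 participants per time point (Sample size estimation) and AD in about 20% (Introduction). Inputs assumed here, because the article does not give them: incidence, persistence, any difference in prenatal prevalence, and two exposure groups of 500.

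Formula, per exposure group:

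postpartum prevalence = prenatal prevalence × persistence + (1 − prenatal prevalence) × incidence

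(a) Onset differs; prenatal prevalence (20%) and persistence (70%) are equal. Incidence is 5% unexposed and 10% exposed, so the true onset ratio is 2.0.
- Unexposed: 0.20 × 0.70 + 0.80 × 0.05 = 0.180
- Exposed: 0.20 × 0.70 + 0.80 × 0.10 = 0.220
- Prevalence ratio: 0.220 / 0.180 = 1.22
- New cases: 500 × (0.04 + 0.08) = 60

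(b) Onset is equal at 6% (true onset ratio 1.0) and persistence is 70% in both. Prenatal prevalence is 15% unexposed and 25% exposed.
- Unexposed: 0.15 × 0.70 + 0.85 × 0.06 = 0.156
- Exposed: 0.25 × 0.70 + 0.75 × 0.06 = 0.220
- Prevalence ratio: 0.220 / 0.156 = 1.41
- New cases: 500 × (0.051 + 0.045) = 48

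(c) Onset is equal at 6% (true onset ratio 1.0) and prenatal prevalence is 20% in both. Persistence is 50% unexposed and 80% exposed.
- Unexposed: 0.20 × 0.50 + 0.80 × 0.06 = 0.148
- Exposed: 0.20 × 0.80 + 0.80 × 0.06 = 0.208
- Prevalence ratio: 0.208 / 0.148 = 1.41
- New cases: 500 × (0.048 + 0.048) = 48

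The prevalence ratio can therefore hide an onset effect (a) or suggest one that does not exist (b, c). In all three cases the same log-binomial model, restricted to people without prenatal AD, targets the onset ratio directly.

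**The case against.** The strongest reply is that the article does not say prevalent cases will be modelled. The outcome is simply called AD, and the wave and at-risk set of an exploratory regression are details that a full analysis plan commonly supplies. The design is a two-wave cohort, the DART records onset, and postpartum incidence is announced, so the investigators may well intend an incident analysis. COVID-19 experience and family work are collected at both waves (Table 1), so earlier exposure values exist, and nothing says that same-wave values will be used. Age and parity, two of the named predictors, cannot be caused by anxiety. On exacerbation, the Discussion mentions predictors of symptoms as well as diagnosis, so a graded outcome may be in mind.

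Much of this stands. A reader might infer that the plan has chosen prevalent AD, or that a binary outcome rules out estimating onset. The document supports neither. It leaves the outcome open, and a binary model of new cases among those initially free of AD does estimate onset.

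The reply does not remove the mismatch in the printed text. The article states the interpretation, development and exacerbation, and pairs it with an outcome that cannot deliver the second and delivers the first only under a restriction that is not stated. A passing mention of symptoms in the Discussion does not define worsening.

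**Conclusion.** The point holds in a limited form. For exacerbation, the stated outcome cannot support the claim, and no section offers another. For development, the claim is supportable only if the model is confined to new cases among people free of AD prenatally, which Additional analysis does not say. Fitted to current AD in everyone, it would give a prevalence ratio mixing onset with persistence.

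The size of any distortion is unknown. The values 1.22 against a true 2.0, and 1.41 against a true 1.0, rest on assumed incidence, persistence and group differences. They show that the error can go either way, not how large it will be in this study.

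It would be going too far to conclude that the study cannot examine onset; its design can. The analysis is secondary and exploratory and does not touch the screening-accuracy objective, so severity is low.

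**What to change.** - **Development.** Fit the log-binomial model to new postpartum AD among participants without AD at the prenatal interview. Take exposures from the prenatal questionnaire and use the DART onset item to confirm that the disorder is new. The announced postpartum incidence needs this same at-risk set.
- **Exacerbation.** Either model change in a severity or symptom measure recorded at both waves among those with prenatal AD, or drop the term. DART severity can serve only if it is recorded for participants, which the article does not say.
- **Models on all participants.** Report them as prevalence ratios and word them as association with AD, in line with the objectives and the Discussion.

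The cost is mainly wording in the analysis plan. Data collection is still under way, but the two interviews, the onset item and the prenatal exposures are already in the design. The statistical price is fewer events: at 20% prevalence and 1,000 per wave, about 1,000 × (1 − 0.20) = 800 participants would be free of any AD, and the assumed rates above give only 48 to 60 new cases. Exposures that arise only after birth, such as care of the new baby, have no prenatal value. Their results should stay worded as association unless the onset item shows that the disorder came later.

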## Introduction

For many health conditions, screening is the first step in a pathway to effective, and in some cases lifesaving, interventions [1–3]. It allows for population level early disease detection thereby identifying those in need of further assessment and ultimately treatment. Further, screening provides significant cost savings [4–8] by ensuring that only those who require more time and labour-intensive diagnostic assessments are offered them [4, 8–10]. Although screening for mental health conditions has been shown to lead to improved mental health even in the absence of a clear pathway to treatment [11, 12], there are still several gaps in screening for mental health conditions in Canada, particularly in the perinatal period [13].

The current edition of the Diagnostic and Statistical Manual of Mental Disorders (DSM-5) [14] includes ten anxiety disorders and several anxiety-related disorders (AD). For the purposes of this research, we have defined AD to include all DSM-5 anxiety disorders as well as two anxiety-related disorders: posttraumatic stress disorder (PTSD) and obsessive–compulsive disorder (OCD) [14]. The AD affect one in five pregnant and postpartum people [15], and are of high importance for perinatal people both due to the fact that they are highly prevalent, but also because they are associated with a range of negative reproductive health outcomes [15–17]. These include: obstetrical (e.g., miscarriage, low birth weight, preterm delivery) [16, 18–21]; fetal and infant (e.g., impaired self-regulation and motor development, and an increased risk for attention-deficit/hyperactivity disorder) [16, 22–28]; and the birthing parent (e.g., postpartum depression, reduced employment capacity, unemployment, and decreased social, emotional and physical functioning) [16, 17, 29–35]. The AD are also associated with significant health care costs and increased health care service utilization [36–39].

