### Sample size estimation

Approximately 44,000 residents of BC give birth each year [86]. We are seeking a sample of 1,000 participants for each of the two study time points. This will provide 80% power to detect AUC for ROC curves ≥ 0.56 as significantly different from 0.5, at a significance level = 0.05; 88% power to detect sensitivity ≥ 0.60 as > than 0.5; and > 99% power to detect specificity ≥ 0.60 as > 0.5. We will be able to estimate the prevalence of low prevalence conditions (e.g., 3%) with 1.5% margin of error and 95% confidence. Of note, we will have 80% power to detect AUC ≥ 0.65; 80% power to detect sensitivity ≥ 0.72; and 99% power to detect specificity ≥ 0.72. Allowing for an anticipated attrition of 15%, we are seeking to recruit 1,200 participants. To have 80% power to detect sensitivity ≥ 0.7; and 99% power to detect specificity ≥ 0.6 for the individual AD, we will need ≥ 30 participants per AD in this sample.

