### Data analysis plan

#### Descriptive statistics

Descriptive information will be presented as means, standard deviations, percentages, and 95% confidence intervals. The diagnostic accuracy of screening tools will be assessed via receiver operating characteristic (ROC) curve analyses within the prevalence sample. AUC values, derived from the ROC curves, represent overall diagnostic accuracy, and will be reported with 95% confidence intervals. Optimal cut-off values for each measure will be determined from ROC analyses and based on maximizing Youden’s *J* index value (see screening tool metrics above). The sensitivity, specificity, PPV and NPV, LR ± , and percent correct classification will also be reported. We will also determine the cut-point associated with 0.75 sensitivity and calculate the corresponding *J* index and specificity (prevalence sample). We will estimate sensitivity and specificity of each of the screening tools for the individual AD.

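### The fallback measure would be validated on the participants who trained it; cut-offs are also scored in the data that chose them, which matters mainly for individual disorders

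*Protocol article*

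**What the plan says.** **Fallback measure.** Additional analysis provides that, if none of the tools is sufficiently accurate, a new measure will be derived by factor analysis, logistic regression and prediction modelling, "using the screening tool items from the first assessment as training, and the second assessment as testing and validation". Study design describes one prospective cohort. Procedures says that "participants are administered questionnaires and an interview at two time points: once prenatally and once postpartum".

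**Cut-offs for existing tools.** Descriptive statistics says: "Optimal cut-off values for each measure will be determined from ROC analyses and based on maximizing" Youden's J. Sensitivity, specificity, predictive values and likelihood ratios are then reported, and no separate sample is named. A second cut-point, the one giving sensitivity 0.75, is read from the same data.

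**How the results are used.** The Introduction sets four minimum criteria: AUC at least 0.8, J at least 0.5, NPV at least 0.8 and LR+ at least 4.0. Research objectives bases recommendations on accuracy and feasibility. Objectives promises the most accurate tool for the disorders as a group and for each one.

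**The concern.** A test set drawn from the training participants shares their persistent disorders and stable response habits with the training data. A model that has partly learned those individuals will look better in them than in new people. If the fallback is needed, it becomes the study's main product, and the word validation would claim more than the design supports.

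The cut-off issue is a related, lesser one. A cut-off picked because it maximises J in a sample gives a J that is on average too high in that sample. Naming the best of nine tools adds a further upward bias. Because J is compared with a fixed line of 0.5, the size of these biases relative to the number of cases decides whether they matter.

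**Working it through.** **1. Number of cases.** Sample size estimation states: "We are seeking a sample of 1,000 participants for each of the two study time points". The Introduction states: "The AD affect one in five pregnant and postpartum people". So 1,000 × 0.20 = 200 cases and 800 non-cases (the 21% also given in the Introduction makes it 210 and 790).

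The plan's own figure confirms this count. It claims "88% power to detect sensitivity ≥ 0.60 as > than 0.5", "at a significance level = 0.05" (stated there for the AUC). Power = Φ[((p1 − p0)√n − z√(p0(1 − p0))) / √(p1(1 − p1))].
- One-sided: Φ[(0.10 × 14.142 − 1.645 × 0.5) / 0.490] = Φ(1.208) = 88.6%.
- Two-sided, the same formula gives 81.2%.

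The 88% therefore reproduces with 200 cases, one-sided. For a single disorder the plan says "we will need ≥ 30 participants per AD in this sample", so 30 cases is its own minimum.

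**2. Fallback: same people or new people.** Simulation with N = 1,000 and about 20% prevalence. A logistic model is trained at time 1, then tested at time 2 in the same people and in new people. Two inputs are assumed.
- Within-person correlation: 0 to 0.9.
- Number of items: 20, 60 or 141. The listed lengths add up to 31 + 20 + 10 + 10 + 3 + 2 + 7 + 22 + 36 = 141 (PASS, STAI, EPDS, K10, MGMQ, ANRQ-2A, GAD-7, AD-22, PASQ). This is an upper bound.

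| Items | Correlation | AUC, same people | AUC, new people | Excess | J, same people | J, new people |
|---|---|---|---|---|---|---|
| 20 | 0.5 | 0.850 | 0.849 | 0.001 | 0.525 | 0.525 |
| 20 | 0.9 | 0.860 | 0.849 | 0.011 | 0.547 | 0.526 |
| 60 | 0.7 | 0.853 | 0.841 | 0.012 | 0.529 | 0.509 |
| 60 | 0.9 | 0.867 | 0.840 | 0.027 | 0.562 | 0.505 |
| 141 | 0.5 | 0.820 | 0.807 | 0.013 | 0.463 | 0.436 |
| 141 | 0.7 | 0.839 | 0.812 | 0.027 | 0.506 | 0.449 |
| 141 | 0.9 | 0.874 | 0.811 | 0.063 | 0.574 | 0.445 |

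A repeat run gave an AUC excess of about 0 to 0.08. With 141 items and correlation 0.7, J is 0.708 in training, 0.506 at time 2 in the same people and 0.449 in new people. The second wave thus removes most of the overfitting, but in this scenario the remainder straddles 0.5.

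**3. Cut-off chosen and scored in the same data.** Equal-variance binormal scores with true maximum J = 0.45. At the true optimum, sensitivity = specificity = (1 + 0.45)/2 = 0.725, so LR+ = 0.725/0.275 = 2.64; the AUC is 0.801. Ranges run from a 22-level score to a continuous one.

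| | About 200 cases | 30 cases |
|---|---|---|
| Apparent J | 0.455 to 0.470 | 0.481 to 0.510 |
| True J at the chosen cut-off | 0.443 to 0.444 | 0.431 |
| Optimism in J | 0.01 to 0.03 | 0.05 to 0.08 |
| Mean LR+, apparent vs true at that cut-off | about 2.8 vs 2.7 | 3.1 to 3.2 vs 2.8 |

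The choice of cut-off leaves the AUC unchanged (0.801) and moves NPV by about 0.003.

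**4. Naming the best of nine equal tools** (assumed score correlation 0.5 to 0.7). The winner's apparent J is 0.49 to 0.50 against a true 0.444 for any disorder, and 0.56 to 0.57 against 0.436 with 30 cases.

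**The case against.** **The fallback is a contingency, and wave 2 is new data.** It applies only if every tool fails, which the article calls unlikely. Factor analysis comes first, so a 141-item model is not the plan, and the PASQ and MGMQ skip questions. With 20 items the excess is about nil unless stability is high. All of this stands, and it limits the size. It does not turn the same participants into an independent test set. A reader might infer that the new measure is scored on its own training data; it is not.

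**Maximising J is standard, and a correction may sit in an analysis plan not shown here.** This stands: the absence of a correction from an article is not an error in itself. What the article does fix is the decision rule, which compares the in-sample J with 0.5 and names a best tool for each disorder.

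**Other safeguards exist.** Each tool is assessed at two time points, and feasibility also counts. But the false-discovery-rate correction adjusts p-values, not optimism in J, and the 0.75-sensitivity cut-point is also found in the study data.

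**A stronger reading fails.** A reader might infer that in-sample cut-offs usually let an inadequate tool through. With nine tools of true J 0.45, at least one does show J of 0.5 or more in roughly 40 to 64% of studies with 200 cases and 83 to 95% with 30. But a pre-fixed cut-off already gives about 37 to 38% and 76 to 79%, so most of this is sampling error across tools assumed to sit just below the line. The criteria also apply together: J, LR+ and AUC are jointly met by at least one such tool in only about 3 to 9% of studies with 200 cases, and 41 to 59% with 30. For the pooled outcome, LR+ of at least 4 is a real safeguard.

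**Conclusion.** The main point holds on the article's own words: the stated validation of the fallback is a repeat measurement of the training participants, and it should not be called independent. Its optimism in AUC runs from about nil to several hundredths, and the figure depends on an item count and a within-person stability that the article does not give.

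The cut-off point holds as a secondary one. For the pooled disorders the optimism in J is minor. For an individual disorder at the planned minimum of 30 cases it is material relative to the 0.5 line, and larger again for a tool named best. LR+ is affected less, and AUC and NPV essentially not. These sizes assume binormal scores and a true J near 0.45. The documents do not support a claim that all four thresholds are compromised, or that the pooled results are seriously biased.

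**What to change.** **Fallback.** Split by participant, not by wave. Keep both assessments of a person in the same fold (repeated k-fold), or train and test on different participants. Repeat item reduction, modelling and cut-off choice within each training part. If the split by wave is kept, describe the second-wave result as a repeat assessment in the same cohort, not as validation.

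**Existing tools.** Report optimism-corrected J, sensitivity, specificity and LR+ from a participant-level bootstrap that re-selects the cut-off in each resample. Where a tool is named most accurate, repeat that choice inside the bootstrap too, because a tool-by-tool bootstrap leaves the best-of-nine bias in place. Judge the thresholds on the corrected values, at least for individual disorders. Also carry the prenatal cut-off unchanged to the postpartum wave, as a check that the cut-off transfers and not as independent validation.

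**Cost.** No new data: more analysis code, a few sentences, and slightly less favourable reported accuracy.
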